## Methods

### Design

We have designed a cross-sectoral longitudinal study that aims to include 1500 patients undergoing elective surgery. The study employs a stepped-wedge design with cluster randomization of five medical centers. The study will have seven periods, each lasting 12 weeks (see Fig. 1). The study will evaluate an all-encompassing “best practice” multimodal intervention for preventing delirium and POCD that includes six consecutive measurement points: preadmission, preoperative, and postoperative including daily delirium screening for 7 days after surgery and 2, 6, and 12 months after surgery. We aim to show that: the cross-sectoral multimodal and multidisciplinary intervention reduces the delirium rate by at least 40% compared with treatment as usual; the cross-sectoral multimodal and multidisciplinary intervention reduces the rate of postoperative cognitive decline by at least 20% compared with treatment as usual; and the cross-sectoral intervention, including the team training and the modules for nonpharmacological prevention, is cost-effective and therefore the improvement in quality of life imposes no additional costs because the care needs of the patients and caregivers are lower than with the standard treatment.

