
Given the patient-centered care research implementation goal of this study, the outcomes of patients undergoing the intervention will be compared to the outcomes of patients receiving treatment as usual (TAU) provided by the centers before the randomized start of the intervention.

Patient group involvement and staff involvement has been implemented in an earlier version of this intervention approach adapting the HELP (Hospital Elderly Life Program) structure (see [18]). In addition, we will implement focus groups at the general practitioner level post hospital stay to further evaluate patients’ perception of the intervention itself.

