#### Recruitment

The study takes place in Germany in the state of Baden-Württemberg. The study will be performed in university hospitals in Tübingen, Freiburg, and Ulm, and in tertiary care hospitals (one in Stuttgart and two in Karlsruhe). In total, five medical centers (one per city) with 12 surgical departments (three in Stuttgart and Tübingen, and two at the other centers) are included. To balance the surgical subspecialties per center, recruitment is restricted to a maximum of 2/3 from one of the following surgical subspecialties: orthopedics, vessels and cardiac, or abdominal. We intend to maintain this ratio for every center and for every 12-week interval of the study.

Patient recruitment will be carried out by a medical specialist. Study staff, including doctors and scientists, will provide the necessary information and obtain the written informed consent from the patients, and whenever possible also from one relative (to assess the caregiver burden and the cognitive status of the patient).

The medical directors and the managers of anesthesia and nursing at the hospitals included in the study have provided a letter of intent expressing their interest in introducing and evaluating preventive procedures, and their willingness to recruit the necessary number of patients. Hence, the recruiting objective is realistic. However, if a department fails to meet its recruitment target (17 patients for the departments in Stuttgart and Tübingen, 25 patients for the others) during one period, concrete and binding measures will be taken to reach the planned number of patients. In this case, the center will commit either to increase the recruitment in its departments or to include another surgical department. If several departments do not reach their target, then the five recruitment blocks, each lasting 3 months, will be extended to 4 months, adding 33% more time to recruit. In this case, for the patients recruited during the last period of the project, the POCD assessments would be completed after 6 months instead of after 12 months.

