#### Randomization

Randomization will take place at the cluster level (*k* = 5 clusters) using a computer-generated sequence. Five months before starting the intervention in a given center, that center and the training team in Stuttgart will be informed about the allocation to prepare for the training and to form the intervention teams. Otherwise, randomization allocation will only be known to the consortium leader and the scientific staff at the University of Potsdam, who will implement the random sequence generation.

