#### Statistical analysis

For the primary outcome, logistic regression analyses with cluster adjustment are planned.

For the secondary outcomes, the changes in the medication and the care burden of the patients’ relatives, we plan analyses using mixed linear and logistic regression models, with fixed and random factors for estimating heterogeneity over clusters [68].

Subgroup analyses for specific patient groups (e.g., patients with cardiac surgery regarding cognitive status or patients with brief hospital stays/brief surgeries) are planned.

For planned validity assessments of postoperative delirium, the validity of the I-CAM-S and NuDESC vs the RASS will be evaluated as screening tools for postoperative delirium. Diagnostic test performance of the tools will be evaluated by receiver operating characteristics (ROC) analysis.

Missing data (due to nonadherence of a department or a particular patient) will be documented. We will apply mixed-effect models, which handle the missing data without using any imputation method. Mixed-effect models assume that the missing data are missing at random (MAR); that is, when the probability that an outcome is missing is related to some other fully observable variable in the model, but not to the variable with the missing value itself [69].

Regarding the health-economic evaluation, a micro-costing analysis will be carried out using data from the clinical administration of two hospitals (Tübingen and Stuttgart). Moreover, for the patients insured by a specific health insurance (AOK Baden-Württemberg) who consent, the health and care insurance costs of the 12 months before and after surgery will be calculated using a difference-in-difference approach [70]. In this case, the target parameter is the cost per avoided POCD. The cost-effectiveness of the intervention will be calculated comparing the costs of the intervention group and the control group. In addition, quality-adjusted life years (QALYs) will then be calculated using data from the EQ-5D-5 L form about health-related quality of life, and applied for calculating the incremental cost-effectiveness. When possible, subgroup analyses will be carried out, for example, by age or gender, to determine whether cost-effectiveness is different in the corresponding groups. Sensitivity analyses will also be performed. The evaluation will be carried out following the recommendations of the “Good practice secondary data analysis” (GPS).

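### Adding a surgical department mid-trial can change a centre's case mix across its crossover, and the adjustment named for the primary model does not remove this

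*Protocol article*

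**What the plan says.** All references are to the protocol article.

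- Recruitment, starting position: "five medical centers (one per city) with 12 surgical departments (three in Stuttgart and Tübingen, and two at the other centers) are included". Targets per period are 17 patients per department in Stuttgart and Tübingen and 25 elsewhere.
- Recruitment, remedy for a shortfall in one period: "the center will commit either to increase the recruitment in its departments or to include another surgical department". The section does not say when, relative to the centre's crossover, a new department may join, and does not ask it to recruit any control-phase patients.
- Recruitment, case-mix safeguard: "recruitment is restricted to a maximum of 2/3 from one of the following surgical subspecialties" (orthopaedic, vascular and cardiac, abdominal). The intention is to hold this in every centre and every 12-week interval.
- Randomization: "Randomization will take place at the cluster level", with five clusters. Departments are not randomised.
- Intervention, comparator: "treatment as usual (TAU) provided by the centers before the randomized start of the intervention".
- Statistical analysis: "For the primary outcome, logistic regression analyses with cluster adjustment are planned". No department, subspecialty or period term is named.

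**The concern.** In this design a centre's patients before crossover are the controls for its patients after crossover. The comparison is fair only if the two groups are alike apart from the intervention and calendar time. A shortfall is visible only once a period has run, so an added department starts in period 2 at the earliest and tends to fall more on the intervention side than the initial departments do. The Background section names the surgical procedure among the triggers of delirium, so a new department may well have a different delirium risk.

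If the new department has lower risk, its arrival looks like prevention. If it has higher risk, it hides prevention. A centre term compares patients within a centre, and that is where this change of mix takes place. The cap limits the mix in each interval but does not require it to be equal before and after crossover.

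**Working it through.** **Layout (assumption, because Fig. 1 is not shown).** The Design section states "The study will have seven periods, each lasting 12 weeks". I take five steps, one crossing centre per step, and one non-recruiting training period per centre. Centre *i* is then control in periods 1 to *i*, in training in period *i*+1, and under intervention from *i*+2 to 7. This agrees with the protocol's own figures: 3 × 17 = 51 and 2 × 25 = 50 patients per centre-period, against the stated maximum of 50; and 5 centres × 6 recruiting periods × 50 = 1500, the planned total.

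**Exposure of an added department.** Recruiting centre-periods that remain from the start period onward, summed over the five centres:

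| Start period | Control | Intervention | Share under intervention |
|---|---|---|---|
| 1 (initial departments) | 15 | 15 | 15/30 = 50% |
| 2 | 10 | 15 | 15/25 = 60% |
| 3 | 6 | 15 | 15/21 = 71% |
| 4 | 3 | 14 | 14/17 = 82% |
| 5 | 1 | 12 | 12/13 = 92% |
| 6 | 0 | 9 | 100% |
| 7 | 0 | 5 | 100% |

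Of the 30 combinations of centre (5) and start period (2 to 7), those with no control period number 1 + 2 + 3 + 4 + 5 + 5 = 20. Without the training gap the count is 15 of 25. The exception is a late-crossing centre that adds early: the last centre, adding in period 2, has only 1 of 5 remaining periods under intervention.

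**Size at one centre (specialty rates are assumptions; the documents give none).** Take a two-department centre with one high-risk and one low-risk department of equal size, which adds a second low-risk department of the same size. The high-risk share falls from 1/2 to 1/3, within the cap.

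- Rates 35% and 15%: before, 1/2 × 35 + 1/2 × 15 = 25.0%. After, 1/3 × 35 + 2/3 × 15 = 21.7%. Shift 3.3 points.
- Rates 30% and 20%: before, 25.0%. After, 1/3 × 30 + 2/3 × 20 = 23.3%. Shift 1.7 points.

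The Sample size section plans for a fall from 25% to 15%, or 10 points. Averaged with equal weight over five centres, one such centre shifts the overall rate by 3.3/5 ≈ 0.7 or 1.7/5 ≈ 0.3 points.

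**What each model does.** I fitted logistic models to expected cell means under the layout above, with 50 patients per centre-period, a true odds ratio of 1 and 25% risk in the initial departments. The assumed ranges for the new department are deliberately wide: risk 10% to 40%, share one third to one half of its centre's patients, start in period 3 or 4.

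- Centre terms only, all five centres adding: expected odds ratio 0.68 to 1.37.
- Centre and period terms, all five adding alike in the same period: 1.00.
- Centre and period terms, only the two earliest-crossing centres adding: 0.84 to 1.15.
- Centre and period terms, only the last centre adding: 0.89 to 1.14.
- Centre, period and added-department terms: 1.00 in every scenario.

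The planned effect corresponds to an odds ratio of (0.15/0.85)/(0.25/0.75) = 0.53. In the case with all five centres adding in period 3, a one-third share and 10% risk, the department terms raise the standard error of the log odds ratio from 0.283 to 0.289.

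**The case against.** The strongest reply is that the analysis sentence is one line in a journal article and the analysis plan is not shown. A reader might infer that the primary model will adjust for centre and nothing else. The article does not say so: centre is the only adjustment it names, and an unseen plan may add others. That part of the objection stands. It does not dispose of the point, because the recruitment rule is fixed in the protocol. Even with a department term, a department that has no control period adds almost nothing to the within-centre contrast, so the rule can restore the headcount without restoring the information.

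Three other stronger readings are tempting and should be set aside.

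- That added departments always recruit mainly under intervention. The first period can trigger the rule, and late-crossing centres that add early are an exception. The 20-of-30 count also weights all start periods equally.
- That period terms cannot help. They remove the bias when all centres add alike at the same time. The article ties the addition to under-recruitment, not to crossover.
- That the shift could be 6.7 points. That figure comes from moving from 2/3 to 1/3 high-risk patients at rates of 35% and 15% (28.3% to 21.7%). The cap permits such a move without any added department, so it does not measure this rule.

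It is also true that a new department of the same subspecialty as the failing one may restore the planned mix, and that the option may never be used.

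**Conclusion.** The point holds as a conditional risk. The protocol permits a change of case mix within a centre that can coincide with crossover, its cap does not prevent this, and the one adjustment it names does not remove it. Bias requires that the option is used, that the new department's delirium risk differs, and that the analysis does not separate departments. Its direction cannot be foreseen.

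One low-risk addition to a two-department centre moves that centre's rate by 3.3 or 1.7 points under the assumed specialty rates, and the overall rate by less if few centres add. The odds-ratio range of 0.68 to 1.37 is an outer case: all five centres add and the model has centre terms only. The exposure shares rest on the assumed layout. The documents do not support saying that the primary result will be biased. They do support a cheap safeguard.

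**What to change.** 1. In the primary model, include department alongside centre and period. If that is too fine, use at least surgical subspecialty, which has to be tracked for the cap anyway. Subspecialty is the weaker choice because it does not separate departments within a group.
2. Add a sensitivity analysis limited to the 12 initial departments, or to departments with patients in both phases of their centre.
3. State in the Recruitment section that, where possible, an added department should join before its centre's crossover. A strict ban on later additions is not needed and would largely close the option to early-crossing centres.

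Cost: two sentences in the analysis plan and one in the recruitment rule; a very small loss of precision from the department terms (0.283 to 0.289 in the case calculated, with period terms already in the model, so their own cost is not counted here); and somewhat less freedom in recruitment at a struggling centre.

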#### Randomization

Randomization will take place at the cluster level (*k* = 5 clusters) using a computer-generated sequence. Five months before starting the intervention in a given center, that center and the training team in Stuttgart will be informed about the allocation to prepare for the training and to form the intervention teams. Otherwise, randomization allocation will only be known to the consortium leader and the scientific staff at the University of Potsdam, who will implement the random sequence generation.

#### Data management

The collection of the clinical data during all stages of the study (preadmission, admission and postoperatively) will be performed exclusively by authorized staff of the study sites, using electronic Case Report Forms (eCRFs) via the web-based electronic data capture (EDC) system secuTrial® from interActive Systems GmbH. The access to the secuTrial® platform is protected by an authentication process, and the transmission of data between the study centers and the secuTrial® server is protected by a secure connection using Secure Sockets Layer (SSL) encryption. All collected data will be checked for reliability and validity every 3 months. Data access will be granted initially to project and data management and consortium leaders. All the data from scales and neuropsychological tests, as well as the clinical data and the data for the health-economic analysis, will be stored in a pseudonymized fashion. After the end of the study, all paper and electronic documents will be stored for at least 10 years more.

#### Statistical analysis

For the primary outcome, logistic regression analyses with cluster adjustment are planned.

For the secondary outcomes, the changes in the medication and the care burden of the patients’ relatives, we plan analyses using mixed linear and logistic regression models, with fixed and random factors for estimating heterogeneity over clusters [68].

Subgroup analyses for specific patient groups (e.g., patients with cardiac surgery regarding cognitive status or patients with brief hospital stays/brief surgeries) are planned.

For planned validity assessments of postoperative delirium, the validity of the I-CAM-S and NuDESC vs the RASS will be evaluated as screening tools for postoperative delirium. Diagnostic test performance of the tools will be evaluated by receiver operating characteristics (ROC) analysis.

Missing data (due to nonadherence of a department or a particular patient) will be documented. We will apply mixed-effect models, which handle the missing data without using any imputation method. Mixed-effect models assume that the missing data are missing at random (MAR); that is, when the probability that an outcome is missing is related to some other fully observable variable in the model, but not to the variable with the missing value itself [69].

Regarding the health-economic evaluation, a micro-costing analysis will be carried out using data from the clinical administration of two hospitals (Tübingen and Stuttgart). Moreover, for the patients insured by a specific health insurance (AOK Baden-Württemberg) who consent, the health and care insurance costs of the 12 months before and after surgery will be calculated using a difference-in-difference approach [70]. In this case, the target parameter is the cost per avoided POCD. The cost-effectiveness of the intervention will be calculated comparing the costs of the intervention group and the control group. In addition, quality-adjusted life years (QALYs) will then be calculated using data from the EQ-5D-5 L form about health-related quality of life, and applied for calculating the incremental cost-effectiveness. When possible, subgroup analyses will be carried out, for example, by age or gender, to determine whether cost-effectiveness is different in the corresponding groups. Sensitivity analyses will also be performed. The evaluation will be carried out following the recommendations of the “Good practice secondary data analysis” (GPS).

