#### Sample size

The power analysis for the primary outcome of delirium prevalence assumes a reduction in the outcome from 25% to 15% [20] as a result of the intervention. A conventional analysis to detect differences in proportions (delirium rate) between the intervention and control groups, using Fisher’s exact test, results in a total of 514 patients with a 1:1 randomization, given a power of 1 – β = 0.80 and an α error of 5%. Using the adjustment form proposed by Woertman et al. [67] with five crosspoints in a stepped-wedge design, with a maximum of 50 patients per cluster per period and an intracluster correlation of 0.01, leads to a correction factor for the stepped-wedge design of KF = 2.63, and therefore a number of 514 × 2.63 = 1351 patients. Assuming a dropout rate of 15%, this leads to a total requirement for about 750 patients per arm. The minimum number of clusters is given by the ratio of the total number of patients to the product between the number of crossing points and the patients per cluster per period, and is 15.

For the secondary outcomes, a reduction of the persistent cognitive deficit from 20% to 10% results in 428 patients using the conventional analysis with Fisher’s exact test and a 1:1 randomization, a power of 1 – β = 0.80, and an α error of 5%, which after the design correction leads to a requirement of 1079 patients.

Thus, the planned sample size is of at most 1500 patients (see Fig. 1 with the numbers per period). Furthermore, relatives of the patients will be asked about the burden of caring and the cognitive status of the patients.

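### The primary model names cluster but no calendar-period term, although treatment follows control in time in every centre and the sample size was calculated as if period were fitted

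*Protocol article*

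**What the plan says.** The Design section states: "The study employs a stepped-wedge design with cluster randomization of five medical centers". It adds: "The study will have seven periods, each lasting 12 weeks". Under Intervention, the comparator is usual care "provided by the centers before the randomized start of the intervention", so within a centre every control patient is treated earlier than every intervention patient.

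Under Statistical analysis, the primary model is given in one sentence: "For the primary outcome, logistic regression analyses with cluster adjustment are planned". The secondary outcomes get mixed linear and logistic models "with fixed and random factors for estimating heterogeneity over clusters". Neither sentence mentions period, step or calendar time, and no other section names such a term for a clinical outcome.

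The Sample size section takes 514 patients for an individually randomised 1:1 comparison of 25% with 15%. With five crossing points, at most 50 patients per cluster and period, and an intracluster correlation of 0.01, this "leads to a correction factor for the stepped-wedge design of" 2.63, hence 1351 patients before dropout.

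**The concern.** Randomising the order in which centres cross over does not separate treatment from time within a centre. That separation comes from comparing centres that are in different conditions during the same period, and the analysis uses this only if period is in the model. With cluster alone, any drift in surgical or anaesthetic practice, delirium awareness, case mix or season is partly read as an effect of the programme.

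What is at stake is the validity of the primary test. A falling background rate inflates the apparent benefit and the false-positive rate. A rising rate hides part of a real benefit.

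**Working it through.** **Inputs.** From the Sample size section: 25% and 15%, 514 patients, 50 per cluster-period, intracluster correlation 0.01, five crossing points, factor 2.63, dropout 15%. From Design: five centres. Assumed: six recruiting periods, because 5 × 6 × 50 = 1500, the planned total. Design speaks of seven periods and Recruitment of five recruitment blocks, so the grid is an assumption. A two-sided 5% level is also assumed.

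**1. The plan's own factor.** The design effect per measurement, with k = 5 steps, one baseline period, one period per step, n = 50 and ρ = 0.01, is

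[1 + ρ(kn + n − 1)] / [1 + ρ(kn/2 + n − 1)] × 3(1 − ρ) / [2(k − 1/k)]
= (3.99 / 2.74) × (2.97 / 9.6) = 0.4505.

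Times six periods this is 2.70. The plan states 2.63, which the same formula gives at 40 per cell. 514 × 2.70 is about 1389 against the stated 1351, a difference of 2.8%. The plan's figure is therefore reproduced closely.

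**2. Which model does that factor belong to?** The generalised least-squares variance of the treatment effect (5 centres × 6 periods × 50, ρ = 0.01), relative to individual 1:1 randomisation of 1500, is:

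| Centre effects | Without period | With period |
|---|---|---|
| Random | 1.19 | 2.70 |
| Fixed | 1.27 | 3.18 |

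The fixed-centre value without period can be checked by hand. The information is the sum of 50·s(6 − s)/6 over s = 1 to 5, which is 50 × 35/6 = 291.7, against 375 for 1:1. Then 375/291.7 × 0.99 = 1.27. Nothing near 2.63 appears without period effects.

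**3. How much of a trend enters the cluster-only estimate.** For a centre crossing after period s, the mean control period is (s + 1)/2 and the mean intervention period is (s + 7)/2. The difference is 3 in every centre. Six periods span five intervals, so with fixed centre effects 3/5 = 60% of a linear change enters the estimate. With random centre effects the weight is 2.80 intervals, or 56%. A fall of 1 point per period thus gives a spurious benefit of about 3 points, against a planned difference of 10.

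**4. Consequence for the test.** Simulated logistic regression with centre effects fitted; the drifts are assumed:

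| True effect | Drift per period | Cluster only | Cluster + period |
|---|---|---|---|
| None | 0 | OR 1.00, about 5% rejected | OR 1.00, about 5% |
| None | −1 point | OR 0.84, roughly 25% | OR 1.00, about 5% |
| None | −1.5 points | OR 0.76, roughly 46% | OR 1.00, about 5% |
| None | +1 point | OR about 1.16, roughly 20% | OR 1.00, about 5% |
| OR 0.53 | −1 point | OR 0.45 | OR 0.53 |
| OR 0.53 | +1 point | OR 0.61 | OR 0.53 |

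Rejection rates for the two downward drifts vary by a few points between simulation runs; the odds ratios are stable.

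**5. Power once period is fitted.** For 25% against 15%, random centre effects give a standard error of 0.034 and about 84% power at 1500. After 15% loss (42.5 per cell) the standard error is 0.0365 and power about 78%. Fixed centre effects give about 78% and 71%.

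**The case against.** The strongest reply is that one condensed sentence in a journal article is not a full model statement. It does not say that cluster is the only term, a list of covariates normally belongs in the analysis plan, and that plan is not shown. The sample size even suggests that the team had a period-adjusted analysis in mind. This stands to the extent that one cannot say the plan rejects period adjustment. It does not remove the point: the article does name its adjustment, and the one it names does not match the model behind its own sample size.

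A reader might also infer more than the documents support:

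- **That the whole of any secular change is credited to the intervention.** For a linear trend it is about 56 to 60%, and the bias can run against the intervention.
- **That a false-positive rate far above 5% is established.** It depends on drifts that are assumed here.
- **That cluster adjustment means robust standard errors, unreliable with five clusters.** The article never mentions them, so there is nothing to criticise on that ground.
- **That leaving out surgical case mix is an error.** The article says "recruitment is restricted to a maximum of 2/3 from one of the following surgical subspecialties" and intends to hold this in every centre and every interval, which limits case-mix drift by design. Adding specialty or other baseline covariates is optional.

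**Conclusion.** The point holds as a mismatch within the protocol article: the stated primary analysis lacks the period term that the design needs and that the sample-size factor presupposes. Two parts rest on no assumed trend: the direction of time within centres, and the comparison of 2.70 with 1.19 (random centres) or 3.18 with 1.27 (fixed centres), given the six-period grid. The 56 to 60% share assumes that grid and a linear trend. The odds ratios and rejection rates also assume the drift sizes shown.

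Because it concerns the validity of the primary test, it should be settled before analysis. If an analysis plan not shown here already fits period, only the wording of the article needs to be brought into line.

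**What to change.** State the primary model as logistic regression with intervention, calendar period as a categorical fixed effect, and a random intercept for centre. Put the same period term in the secondary clinical models. Specify inference suited to five clusters: either a small-sample correction or a permutation check over the 5! = 120 possible centre orders. Covariates for surgical specialty or baseline status may be added but are not required by this point.

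The change is to analysis wording; it needs no new data and no design change. The cost is lower precision than a cluster-only model. The stepped-wedge factor already assumes that cost for random centre effects (about 84% power at 1500, 78% after 15% dropout). It does not cover fixed centre effects (about 78% and 71%), so choosing those instead would need to be acknowledged in the power statement.
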